Although rehabilitation training is the primary treatment method for stroke patients, the current results of rehabilitation for poststroke hand dysfunction are not satisfactory [1]. There is an urgent need to develop more effective and inexpensive rehabilitation techniques for hand function. Mirror therapy (MT) has emerged as a promising new rehabilitation intervention in recent years [5, 6]. MT typically involves placing a flat mirror on the unaffected side of the body, allowing the patient to “embody” their paralyzed limb through the optical illusion created by the mirror. This technique effectively “tricks” the brain into perceiving movement in the affected limb, potentially aiding in the recovery of motor function. MT has shown particular efficacy in the treatment of phantom limb pain [7–9] and has also begun to show promise as a therapeutic approach for stroke [5]. Research has demonstrated that MT is an effective adjunctive therapy for improving upper extremity motor function and daily living among stroke patients [7, 10–12]. A study found that MT combined with bilateral arm training and graded activities was effective in improving motor performance of the paretic upper limb after stroke compared with conventional therapy without MT [13]. We have also done previous studies demonstrating that the combination of conventional rehabilitation therapy and TBMT is an effective way to improve functional recovery in upper limb stroke patients [14] (Fig. 1). However, to date there has been little agreement on the facilitative effect of MT. A randomized controlled trial by Antoniotti et al. found no significant difference between actual and sham MT for functional recovery of the upper extremity in early stroke [15]. There is a strong link between acquisition of motor skills and neuronal plasticity at cortical and subcortical levels in the central nervous system [16]. Therefore, it is possible that these limitations arise from the fact that patients exhibit varying degrees of structural preservation at the injury site, and the treatment of MT effect on upper limb motor function of hemiplegia is somehow dependent on the severity of the lesion, which ultimately resulted in contradictory findings.

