### Sample size estimation

The sample size was derived from pre-existing research using G Power v.3.1, considering significance level (*α*) = 0.05, power (1 − β) = 0.95, and given that the minimal clinically significant difference in patient’s hand function improvement, as per prior study data, is 9 points in the FMA-UE with an effect size of *d* = 1.13 [14]. Estimation via G Power software yielded a requirement of 44 samples. Considering potential subject attrition or termination, the sample size could be augmented by 10–15%, resulting in the adjusted sample size of *N* = 50, or 25 patients in each group. Consequently, the total sample size for both groups was formulated as 50.

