### Statistical analysis

Data management and analysis will be conducted in SPSS version 23. Groups will be compared at baseline using the *t* test for independent samples for the continuous variables, and the chi-square test for categorical data. The differences of the outcomes, including the FMA-UE, MBI, ARAT, and the 9HPT, between the groups at each of the trial time points will be analyzed using mixed-design 2-way repeated-measures analysis of variance (ANOVA), taking time (4 levels: preintervention, after 2 weeks, after 4 weeks of intervention and 3 months at the end of the trial for follow-up) as the within-subject factor and group (2 levels: TBMT and CG) as the between-subject factor. If participants drop out during the intervention period, they will not be excluded due to the principle of intention to treat (ITT). Furthermore, in instances of missing data, the continuation of observations (LOCF) method will be employed, whereby the last recorded observation preceding the gap in data will serve as a substitute. Unfavorable stroke outcomes correspond to lower FA values for corticospinal tracts, while robust functional recovery denotes elevated FA values. Subgroup analyses of FA values will be conducted based on the interquartile spacing (< 25% interval; 25–75% interval; > 75% interval) method post the inclusion of all individuals to standardize the baseline conditions of the patients. We will use linear regression model outcomes at 4 weeks post-treatment cessation as the dependent variable (FMA-UE). This model will include treatment assignment (TBMT vs. CT) and baseline outcome measure as fixed-effects, as well as patient characteristics (low or high impairment severity at baseline). We will examine differential impacts by fitting separate models with treatment-impairment severity. We will report relevant point estimates and standard errors for these models and conduct 5% level tests for interaction terms with two-sided alternative hypotheses. A *p*-value < 0.05 is deemed a statistically significant discrepancy.

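### Testing treatment-by-severity on a low/high split, rather than on a continuous severity score, gives up power for the interaction if the effect changes gradually with severity

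*Protocol article*

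**What the plan says.** The Statistical analysis section of the Protocol article describes a linear regression with FMA-UE as the dependent variable. Its terms are treatment, the baseline outcome measure and "patient characteristics (low or high impairment severity at baseline"). Effect modification comes next: "We will examine differential impacts by fitting separate models with treatment-impairment severity". The interaction terms are to be tested at the 5% level, two-sided.

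Three other places bear on this:

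- Primary outcomes presents FMA-UE (0 to 66) as the measure of upper-limb motor impairment. Table 1 admits patients scoring below 47.
- The Introduction gives as a possible reason for conflicting earlier results that "the treatment of MT effect on upper limb motor function of hemiplegia is somehow dependent on the severity of the lesion".
- Sample size estimation covers the main between-group comparison only. The minimal clinically significant difference "is 9 points in the FMA-UE with an effect size of *d* = 1.13", with "power (1 − β) = 0.95", leads to "Estimation via G Power software yielded a requirement of 44 samples", raised to 50. No power is given for an interaction.

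**The concern.** The interaction is the only term in this model that addresses whether some patients benefit more than others. Coding severity as low or high treats all patients within a half as alike and treats two patients just either side of the cut as different. The model keeps the baseline outcome measure as a covariate, so its prognostic information is retained; only the interaction is coarsened.

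If low/high is cut from FMA-UE, the severity main effect also largely repeats a covariate already in the model.

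What is at stake is the chance of detecting a graded dependence on severity, in a trial sized only for a large main effect. That makes an avoidable loss worth removing.

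**Working it through.** **1. Reproduce the stated sample size.** Inputs from Sample size estimation: d = 1.13, alpha 0.05, power 0.95. A two-sided two-sample t test (noncentral t) needs 22 per arm, total 44, with actual power 95.6%. This matches the stated 44. The implied SD is 9 / 1.13 = 7.96 points. A total of 50 allows for a loss of 1 − 44/50 = 12%. The sample size is not in question.

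**2. Information kept by a median split.** For effect modification linear in severity, the relative efficiency is the squared correlation between the score and its split.

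- Normal score: 2/π = 0.64, so 50 × 0.637 = 31.8 patients.
- Uniform score: 0.75, so 50 × 0.75 = 37.5 patients.

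If the split is made on FMA-UE, the variance inflation of the severity main effect beside the continuous score is 1/(1 − 0.637) = 2.75 (normal) to 1/(1 − 0.75) = 4.0 (uniform).

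**3. Power for the interaction, by simulation.** Two models were compared, each with a two-sided 5% test of its last term:

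- split: outcome = treatment + baseline + low/high + treatment × low/high, cut at the median;
- continuous: outcome = treatment + baseline + treatment × baseline.

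From the article: N = 50, 1:1 allocation, test level, residual SD 7.96 and the entry limit of 46 on baseline FMA-UE. Assumed, because the article does not give them: the median cut, the baseline distribution (uniform on 0 to 46, or roughly normal with SD about 10) and the slope of the effect on baseline.

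| Slope (points of effect per FMA-UE point) | Uniform: split / continuous | Normal: split / continuous |
|---|---|---|
| 0.2 | 17% / 22% | 10% / 13% |
| 0.4 | 47% / 60% | 26% / 39% |

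A slope of 0.4 is steep: over 46 points the effect changes by 0.4 × 46 = 18.4 points, about twice the 9-point design difference. A slope of 0.2 gives 0.2 × 46 = 9.2 points.

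A second set in standardised units (residual SD 1, baseline slope 0.7, 4,000 runs per cell, N = 50):

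| Interaction (SD of outcome per SD of baseline) | Normal: split / continuous | Uniform: split / continuous |
|---|---|---|
| 0.3 | 13% / 17% | 14% / 18% |
| 0.565 | 31% / 47% | 35% / 46% |
| 0.8 | 54% / 75% | 63% / 78% |
| 1.13 | 82% / 96% | 88% / 96% |

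The smallest gap in the two tables is 13 − 10 = 3 points and the largest is 75 − 54 = 21, hence roughly 3 to 20 points. At N = 44 with an interaction of 0.565 and a normal baseline, the figures are 26% and 41%. With no true interaction, both models reject about 5% of the time.

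**4. When the ranking reverses.** If the true effect is a step exactly at the cut (0.565 SD either side, normal baseline, N = 50), the split has 49% power and the continuous test 32%.

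**The case against.** Several objections carry weight.

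- **The scale is not stated.** A reader might infer that low/high is certainly a cut of FMA-UE. The article does not say so. Primary outcomes supports that reading, but the Introduction and the imaging sections also use severity for the lesion and for corticospinal tract damage, and the sentences just before the regression concern FA values. This stands. The redundancy with the baseline score therefore holds only under the FMA-UE reading. The information loss applies to any graded scale.
- **The rationale is structural.** The Introduction ties the varying effect to the lesion, so insisting on baseline FMA-UE as the modifier could replace the intended question with another. This stands, and the fix must allow both readings.
- **The cut-point.** A reader might infer that the cut will be picked after the data are seen. The article prints no cut-point, but such a detail may sit in a full protocol or analysis plan that is not shown, so its absence is not an error.
- **Small interactions.** With a weak interaction both tests have low power (13% against 17%), and sample size is the binding limit. This is true, but the gain costs nothing to obtain.
- **Shape of the effect.** A step at the cut favours the split. This is correct, but the article neither states nor justifies such a threshold.

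**Conclusion.** The point holds as a weakness in a stated secondary analysis. Under graded effect modification, a median split keeps about 64% to 75% of the information on the interaction and costs roughly 3 to 20 percentage points of power at N = 50. The direction rests on the effect changing gradually with severity. The size rests on an assumed slope, baseline distribution and median cut.

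It would be wrong to read this as a flaw in the trial's main result. The split does not raise the false-positive rate at a fixed cut, and it affects neither the repeated-measures comparison of FMA-UE nor the sample size of 50. It is a change worth making because it is nearly free and the interaction has no stated power.

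**What to change.** State which severity is meant and keep it continuous in the interaction test.

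- If clinical impairment: FMA-UE outcome = treatment + centred baseline FMA-UE + treatment × centred baseline FMA-UE, dropping the low/high main effect.
- If structural severity: FMA-UE outcome = treatment + baseline FMA-UE + continuous corticospinal tract rFA (or FA) + treatment × that measure.

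Test the single interaction, two-sided at 5%. Report the treatment effect with a confidence interval at a few severity values set in advance. Keep low/high groups for display only, at a cut fixed beforehand.

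The cost is a change of wording, since the scores and imaging measures are already planned. The drawback is that the test assumes a roughly linear trend and would lose power if the true modification were a step exactly at the cut-point.

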### Patient and public involvement

Although patients cannot directly participate in the design process of clinical trials, they can offer valuable input during the recruitment and informed consent phase. Their views can enhance transparency and fairness, ensuring that patients fully understand the purpose, risks, and advantages of the trial. We prioritize regular feedback and evaluation from patients and assess their satisfaction with the trial process each time to ensure that their voices are heard and to identify necessary improvements. The outcome measures to be evaluated in this study will potentially be influenced by the sociodemographic characteristics and preferences of the patients. Therefore, we use a comprehensive assessment. The result of our study will be published in a peer-reviewed journal.

### Modification of the protocol

Any modifications to the protocol, including changes in objectives, design, patient population, sample size, and study procedures will require a formal application from the Institutional Review Board (the Board) and Hospital Research Ethics Committee (the Committee) of the Second Affiliated Hospital of Chongqing Medical University. Based on safety assessment data, if research is changed to eliminate an apparent immediate danger(s) to the subject, the investigator will promptly notify the Board and the Committee on Change(s). Review by the Board and Committee at the next meeting convened to determine whether the proposed change(s) are consistent with the subject’s continued welfare.

### Data management and quality

Only researchers who participated in this study can access the data. Each participant will receive an ID number for privacy during the trial period. Details are captured on custom case report forms (CRFs) that undergo double checking for accuracy and completion. Associated documents obtain unique code numbers then securely stored within the Rehabilitation Medicine Division of the hospital. Hard copies are transferred to an Excel spreadsheet for review by two doctors before storage on a password-protected computer. Only the lead researcher and statistician hold passwords to this document cabinet, adhering to medical record retention laws and GCP principles. Two additional healthcare professionals will undertake periodic physical site audits to confirm meticulous adherence to the investigative protocol and data accuracy. Through these strategies, we augment patient cooperation and decrease instances of dropout.

## Discussion

Hand function is a key issue in stroke rehabilitation. While there are various treatment options, the availability of precise and effective methods remains a major challenge. Mirror therapy is a relatively effective therapeutic intervention [14]. However, previous studies have not linked functional recovery to the structural basis preserved by the lesion. This may be a potential reason why different teams in the current mirror therapy study have reached opposite results [42]. Therefore, it is imperative to establish high-quality evidence to support the use of mirror therapy in stroke rehabilitation. To address this gap, this is the first study to incorporate comprehensive patient baseline data while considering structural preservation and utilized a customized ergonomic therapeutic device. The primary aim of this study is to assess how effective MT is in rehabilitating stroke patients.

MT is based on the mirror neuron system and uses the plane mirror imaging principle for the contralateral activity images projected on the affected side. It also combines optical illusions, visual feedback, and virtual reality [43]. This visual stimulus supports motor rehabilitation by capitalizing on the strong connection between visual input and the pre-motor cortex [44]. A recent clinical study concluded the neural mechanisms of motor imagery training (MIT) in stroke rehabilitation by fMRI. The conclusion was drawn that MIT helps reduce compensatory activation in both hemispheres in stroke patients, remodels FC in the ipsilateral hemisphere, and promotes functional recovery [45]. However, there is a relatively small body of literature that is concerned with the neural mechanisms of mirror therapy in depth. In this study, we will focus on analyzing the Pearson correlation coefficients between two specific brain regions. We will also investigate the differences in topological properties and lateral connections within the brain network of both intervention and control groups. By doing so, we aim to identify any characteristic manifestations of brain network changes resulting from mirror treatment. This will enable us to better understand the neurological mechanism behind improved hand function through mirror treatment. Meanwhile, we will use an array of assessment techniques to determine the effectiveness of TBMT, including autonomic control (FMA), arm and hand motor recovery (Brunnstrom phase), manual dexterity (9HPT), and daily activities. This study is extremely comprehensive, as you can observe.

In conclusion, this will be a well-controlled, high-quality clinical study, and the findings may be used to update evidence-based protocols in postacute stroke care planning and to translate evidence into practice and medical decision-making.

## Data Availability

Not applicable.

## Abbreviations

DTI: Diffusion tensor imaging
FMA-UE: Fugl-Meyer Assessment Upper Extremity Scale
MBI: Modified Barthel Index
ARAT: Action Research Arm Test
9HPT: Nine Hole Peg Test
TBMT: Task-based mirror therapy
MT: Mirror therapy
CST: Corticospinal tract
fMRI: Functional magnetic resonance imaging
BOLD-fMRI: Blood oxygenated level dependent functional magnetic resonance imaging
OT: Occupational therapy
FA: Fractional anisotropy
rFA: Relative fractional anisotropy
ROI: Region of interest
FC: Functional connectivity
EPI: Echo-planar imaging
DPARSF: Data Processing Assistant for Resting-State fMRI
SPM: Statistical Parametric Mapping
MNI: Montreal Neurological Institute
GCP: Good Clinical Practice
MIT: Motor imagery training
